### 2.21. Randomization

Patients were randomly assigned in a 1:1 ratio to the intervention or control group through permuted-block randomization with varying block sizes. Randomization lists were center-specific and they were created using SAS^®^ Proc Plan permuted-block randomization. A list was created for each center. The lists were created with block sizes of 2, 4, and 6. The order of block permutations was then randomized within each list to avoid predictability. A seed was set for generating the list so that it could be reproduced if necessary. Patient allocation was performed via a centralized email system.

### 2.22. Data Collection and Statistical Analysis

Study data were collected in the eCRF of an electronic web-based database, where each patient is identified by a randomly assigned alphanumeric code that is center-specific.

Baseline data were analyzed through descriptive analyses. Results for the overall population and for both Groups A and B are presented. Categorical variables were presented as frequencies and percentages and compared between the two groups by Chi-square test of Fisher’s exact test. Continuous variables were summarized by mean ± standard deviation and tested for normality distribution by Kolmogorov–Smirnov test. Since all variables were not normally distributed, the non-parametric Wilcoxon–Mann–Whitney U test will be used to compare baseline variables between groups. The prevalence of frail patients in the two groups is indicated as an EFT score ≥ 3. For the planned analyses, mixed models, adjusted for unbalanced variables, will be used to account for different times to follow-up. Only people with available measures of EFT at both baseline and follow-up will be included in the analyses relative to the prevalence of frailty and EFT as a continuous variable, while only individuals with available measures of SPPB at both baseline and follow-up will be included in the analyses for this endpoint. For the other covariates, missing data will be imputed through regression models. Given the limited sample size, subgroup analyses are not planned.

All analyses were performed by using SAS Software version 9.4. Tests will be considered significant for a *p* value < 0.05.

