## 1. Introduction

Older people with cardiovascular disease (CVD) are particularly vulnerable, exhibiting both high mortality [1] and a consistent risk of disability following hospitalization [2]. A major determinant of such poor outcomes is frailty, a clinical syndrome highly prevalent among older individuals with CVD [3]. Frailty is characterized by a progressive decline in the physiological reserves of multiple organ systems, which limits the individual’s ability to cope with stressors and predisposes them to negative health trajectories. As an independent predictor of autonomy loss, frailty is strongly associated with adverse clinical outcomes, including hospital readmissions, institutionalization, and death [4].

Preliminary evidence suggests that frailty may not represent an irreversible condition, raising the possibility that targeted interventions could improve resilience and potentially alter the course of the syndrome [3]. Cardiac rehabilitation (CR) programs are established as effective tools to improve cardiovascular prognosis and quality of life [5]. However, despite their proven efficacy, the uptake of CR remains suboptimal, with older and frail patients facing the greatest barriers due to mobility limitations, comorbidities, and thus a limited access to structured programs. In this respect, digital health interventions offer the opportunity to extend the reach and adaptability of traditional models. By facilitating adherence, enhancing accessibility, and supporting individualized care, eHealth-based CR programs, which incorporate tele-rehabilitation (TR) and remote monitoring, have the potential to overcome many of the barriers encountered by older patients [6]. However, few studies have explored the efficacy of eHealth home-based CR interventions on frailty. Indeed, a recent systematic review concluded that more studies are needed to define its efficacy and usefulness to make definitive recommendations [7].

To fill this gap, we undertook a randomized trial to evaluate whether an eHealth home-based CR intervention, compared with the standard of care, is able to reduce the rate or the degree of frailty in people ≥ 65 years and with acute heart failure (AHF) and/or acute coronary syndrome (ACS). Here we report the protocol of the trial and the baseline clinical data of included participants.

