### 2.2. Study Endpoints

#### 2.2.1. Primary Endpoints

The primary endpoint is to assess whether a home-based TR program significantly reduces the prevalence of frailty in comparison to usual care in older individuals hospitalized for ACS and/or AHF. Frailty status is defined as having an Essential Frailty Toolset (EFT) score (ranging from 0 to 5) ≥ 3 [8].

Since the recent literature suggests that frailty is a progressive continuum and not a present/absent condition [9,10] and considering that small improvements in the degree of frailty are associated with tangible benefits [11], the mean degree of frailty was considered as a co-primary endpoint. In particular, mean differences between groups at the end of treatment in the EFT and Short Physical Performance Battery (SPPB) scales were set as co-primary outcomes after the start of the enrollment due to the considerations reported above. After termination of the enrollment, we observed that the study is powered to detect a difference in these co-primary outcomes, while the power for the primary outcome of frailty prevalence is lower than initially planned. Thus, this and the other secondary endpoints will be considered as exploratory.

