### 2.19. Exercise Training Protocol

All included individuals were subjected to the Short Physical Performance Battery (SPPB) to also evaluate balance and fall risk; based on the result obtained, they subsequently carried out a Six-Minute Walk Test (6MWT) to evaluate their functional capacity. The subjects were thus categorized into two groups based on the tests results: low level or high level (Figure 2). Subjects unable to perform a 6MWT for clinical and/or functional reasons performed only the SPPB.

The program included daily 30 min moderate-intensity aerobic training using a pedal exerciser and twice-weekly 30 min strength training using adjustable dumbbells and ankle weights according to the low- or high-intensity categorization of the individual (Supplementary Table S2).

The patients undertook daily aerobic training sessions using a pedal exerciser, as well as strength training using ankle weights and dumbbells adjustable from 0.5 kg to 2.5 kg, twice a week on non-consecutive days for 30 min per session.

The loads were modulated by monitoring heart rate and the Borg scale, ensuring patients were receiving pharmacological therapy and verifying the absence of adverse symptoms. The treatment program was delivered via tele-rehabilitation using a dedicated platform.

For the high-level exercise group, the intensity was tailored to 70–80% of the theoretical maximum heart rate and with a Borg score of 3 to 5 on the CR10 scale, as this is more easily understood than the Borg RPE scale.

For the low-level exercise group, the targets were lower: 40–70% of the theoretical maximum heart rate, but with the same weekly frequency, starting with 10 min per session and increasing to 30 min if tolerated.

The intensity of the exercises was reassessed at every session, i.e., twice a week.

REMOTE PHYSIOTHERAPY TREATMENT PROTOCOL

Connect online with the patient via the platform;Instruct the patient to wear the monitoring devices the patient has previously been trained to use;Take the basal parameters with the patient sitting at rest for at least 5 min: detect heart rate, peripheral saturation, basal pressure and subjective sensation of effort using the Borg CR10 scale and enter them into a specific database;Remote training with exercises based on FITT principles: frequency, intensity, time, type and progression of the exercise according to the patient’s functional level;Take vital signs at the end of the session with the patient seated.

LOW LEVEL

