## 3. Results

From May 2024 to December 2025, 589 individuals were assessed for eligibility at the two centers. Among them, 147 patients were excluded because they met the exclusion criteria: more than one third (39%) were unable to use electronic devices and 21% were clinically unstable. Among the minor reasons for exclusion were MMSE < 15 (6%) and age < 65 years (4%). Therefore, we screened 442 individuals with recent ACS and AHF who fulfilled the inclusion criteria and were considered eligible for the trial. Among those eligible, 233 declined to participate in the study while two individuals could not be enrolled because they died during hospitalization. The most common reason for declining participation in the trial was the perceived complexity of being compliant with a demanding program, or the willingness to learn how to use the dedicated eHealth platform, a motivation cited by 46% of the eligible individuals approached. Overall, 19% complained about the lack of a caregiver. The remaining 209 people were enrolled in the study and assigned to one of the two groups through randomization. Two patients assigned to the control group dropped out before completing exams or questionnaires and one subject in the intervention group died before discharge (Figure 3). We compared included subjects with the subgroup of subjects who declined to participate with complete data about age, sex and type of cardiac event. The included population was representative of the eligible individuals in terms of age and sex but patients who declined were more likely to have a diagnosis of AHF compared with included individuals (58% vs. 42%, *p* = 0.0078).

Among people undergoing randomization, 103 were assigned to the eHealth intervention group and 103 to the standard-of-care control group. The baseline demographic and clinical characteristics of the two groups are presented in Table 1 while the overall characteristics of the population with the relative number of observations for each variable are shown in Table 2. Clinical characteristics were comparable in the two groups, with the exception of sex and SPPB (Table 1). Overall, the mean (±SD) age of the patients was 77 ± 9 years, and 145 subjects (70.4%) were male. The mean BMI was 25.8. More than half of the patients had ACS (55.3%). As expected, most of the people were receiving lipid-lowering medications (77.5%), antiplatelet drugs (56.4%), and one or more anti-hypertensive medications.

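### The both-measurements rule takes patients who die or drop out out of the primary and co-primary comparisons, and the stated 55% power assumes no such loss

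*Protocol article*

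**What the plan says.** Section 2.22 restricts the frailty endpoints to complete pairs:

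- Frailty prevalence and continuous EFT: "Only people with available measures of EFT at both baseline and follow-up will be included in the analyses relative to the prevalence of frailty".
- SPPB: "only individuals with available measures of SPPB at both baseline and follow-up will be included in the analyses for this endpoint".
- Imputation: "For the other covariates, missing data will be imputed through regression models".
- Model: "mixed models, adjusted for unbalanced variables, will be used to account for different times to follow-up".

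The rule covers the endpoints on which the trial now relies. Section 2.2.1 records that "mean differences between groups at the end of treatment in the EFT and Short Physical Performance Battery (SPPB) scales were set as co-primary outcomes" and makes frailty prevalence exploratory because enrolment fell short. Death is counted only in the secondary composites (section 2.2.2).

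The Introduction says "frailty is strongly associated with adverse clinical outcomes, including hospital readmissions, institutionalization, and death". Section 2.20 allows for about 22% dropout. Section 3 reports 209 randomised and 206 described, because "Two patients assigned to the control group dropped out before completing exams or questionnaires and one subject in the intervention group died before discharge". Table 2 gives a baseline SPPB for 171 of the 206, although section 2.19 says that every included individual had the test. The only sensitivity analysis named is propensity-score matching (section 4).

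**The concern.** Having a follow-up score is itself a post-randomisation outcome. If patients without one are set aside, the arms compared are no longer the arms that were randomised. By the protocol's own account frail patients are more likely to die, so the scores lost to death are unlikely to be a random sample.

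Loss may also differ by arm. Only Group A has a demanding programme, with video-calls twice a week and daily exercise (sections 2.18 and 2.19), and section 2.23 lets the investigator withdraw patients for compliance reasons. If frail patients leave the programme, the intervention can look better than it is. If the programme keeps frail patients alive and assessed, it can look worse.

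The planned methods do not repair this. A mixed model can use partly observed patients, but the pairing rule removes them first. ANCOVA, which section 4 names for the degree of frailty, has the same limit. Propensity-score matching deals with baseline imbalance, not missing outcomes.

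**Working it through.** **1. Reproduce the plan's figures.** Inputs from section 2.20: 21% v 34%, 80% power, alpha 5% (taken as two-sided), 1:1 allocation.

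- Per arm, n = [1.960 × √(2 × 0.275 × 0.725) + 0.842 × √(0.21 × 0.79 + 0.34 × 0.66)]² / 0.13² = (1.238 + 0.526)² / 0.0169 ≈ 184.01, rounded up to 185. The total is 370, as stated.
- EFT means 1.25 v 1.95, SD 1.25, 90% power: 2 × 1.25² × (1.960 + 1.282)² / 0.7² ≈ 67.01, rounded up to 68 per arm. The total is 136, as stated.

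**2. Power for prevalence under the rule.** Power = Φ{[0.13 × √n − 1.238] / 0.625}, with n per arm.

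- 206 analysed (n = 103): (1.319 − 1.238) / 0.625 = 0.13, power 55.2%. This is the 55% given in section 4, so that figure allows for no loss to follow-up.
- 22% loss: 206 × 0.78 ≈ 161 analysed, power about 45%.
- 10% and 30% loss: about 51% and 42%.

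Mean EFT (difference 0.7, SD 1.25) still has about 94% power at 161. For that endpoint the problem is possible bias rather than power.

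**3. SPPB.** 206 − 171 = 35 without a baseline value (35 / 206 = 17.0%). At 22% loss, 171 × 0.78 ≈ 133 have both scores. If the 35 are followed up at the same rate, 35 × 0.78 ≈ 27 follow-up SPPB scores would be collected and then discarded.

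**4. How large could the bias be?** The documents give no deaths or follow-up losses by arm, so these are assumed scenarios. True frailty at follow-up is 34% in both arms (no effect), with about 22% missing in each arm. Frailty among completers = p(1 − m_f) / [p(1 − m_f) + (1 − p)(1 − m_n)], where m_f and m_n are the loss among frail and non-frail patients.

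- Group A loses 40% of frail and 13% of non-frail patients; Group B loses 22% of each. A = 0.204 / (0.204 + 0.574) = 26.2%, B = 34.0%: a spurious 7.8 points in favour of the programme.
- The same pattern with the arms exchanged: 7.8 points against the programme.
- The same frailty-related loss in both arms: no difference.

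The range runs from −7.8 to +7.8 points, against a design difference of 13.

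**The case against.** The strongest reply is that none of the bias can be shown. The scenarios are invented, they concern the binary endpoint that section 2.2.1 now calls exploratory, and equal frailty-related loss gives no bias when there is no effect. Follow-up lasts only 3 to 6 months, and patients with a prognosis of six months or less from other conditions are excluded, which limits deaths. Missing-data sensitivity analyses are often left to an analysis plan. All of this stands as a limit on size and direction. It does not remove the point, because the complete-pairs set is a written rule. An unseen analysis plan would have to contradict it, not fill a gap.

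Several stronger readings are tempting but unsupported:

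- *The 35 patients leave every main analysis.* They leave only the SPPB analysis. Table 2 gives baseline frailty status for all 206. Section 2.5 also places the SPPB before randomisation, so excluding them mainly costs precision and does not by itself break the randomised comparison.
- *Baseline SPPB is missing more often in the control arm.* The arm counts are not reported. Solving from the rounded means, (8.71 − 8.27) / (9.11 − 8.27) = 0.524 of 171, gives about 90 v 81 observed, or 13 v 22 missing of 103 each. A chi-square test gives p of about 0.09, and from 0.35 to 0.04 across the rounding range.
- *SPPB falls short because 133 is below 136.* The 136 is the EFT figure. For SPPB, section 2.20 reports only similar results. Even on the EFT inputs, power at 133 is about 90%.
- *Death must count as frailty in the main analysis.* That is a choice of estimand, which the sponsor should make and state.
- *The pre-discharge death is left out of the death composites.* Nothing in the article says so.

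**Conclusion.** The point holds for the analysis set. Followed as written, section 2.22 conditions the prevalence, EFT and SPPB comparisons on survival and on having a follow-up score, in a trial that expects about 22% dropout and describes frailty as linked to death. The documents give neither the direction nor the size of any bias. The 7.8-point figure shows only what one assumed pattern of unequal loss could do.

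Two consequences can be computed, assuming that the 22% applies to those with baseline data. Power for prevalence is about 45% rather than 55%, and the SPPB analysis would hold about 133 patients. The second is a loss of precision and not evidence of bias. The three of 209 randomised patients already outside the reported 206 (1.4%) are few, but they show that the loss has begun.

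**What to change.** - Replace the both-measurements rule in section 2.22 with an analysis of patients as randomised. Either a longitudinal mixed model with baseline and follow-up scores as outcomes, or multiple imputation by arm, would keep everyone with a baseline or follow-up score. Account for all 209 in the patient flow.
- State how death enters the frailty endpoints. A mixed model alone would in effect project scores beyond death, so include at least one sensitivity analysis that counts death as frail, or a worst-rank analysis for the scores.
- Add a delta (tipping-point) analysis for other missing follow-up, and report the complete-pairs result as supportive. Propensity-score matching may stay as an extra, but it does not answer this question.
- Restate the 55% power in section 4 for the number expected to be analysed, and reconcile the 171 baseline SPPB values with the statement in section 2.19.

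The cost is wording and modest programming; clinical outcomes are already collected during follow-up (section 2.5). Section 4 describes some of the models in the past tense. If outcomes have already been examined, the change must be labelled as made after that point.

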### 2.23. Withdrawal from the Study (Or Modified Follow-Up)

A participant may withdraw from the study at any time at their own request, or may be withdrawn at any time at the discretion of the investigator for safety, behavioral, compliance, or administrative reasons.

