## 2. Materials and Methods

### 2.1. Study Design

This is a multicenter, randomized, parallel-group study in older patients with a recent hospitalization for AHF and/or ACS, conducted at two study sites: IRCCS MultiMedica, Sesto San Giovanni (MI), Italy, and Istituti Clinici Scientifici Maugeri IRCCS, Cardiac Rehabilitation Unit of Bari Institute, Bari, Italy. People with AHF or ACS and ≥ 65 years old were randomized into two groups: Group (A), a multidisciplinary eHealth home-based TR program; and Group (B), which received the usual care. After a minimum of 3 and up to a maximum of 6 months, enrolled subjects underwent a new evaluation for frailty. The duration of follow-up was flexible to facilitate participation and adherence. The latest available follow-up will be considered for each individual and mixed models will be used to account for different times to follow-up in the analyses. A summary of study design is presented in Figure 1. Given the nature of the study involving an active intervention only in the group assigned the eHealth arm, the trial was not blinded, i.e., investigators performing the frailty screening both at baseline and follow-up were also involved in the development of the program. The help of a caregiver was allowed but was not mandatory to participate to the study. Caregivers were not in charge of exercise supervision.

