### 2.3. End of Study Definition

The end of the study is defined as the date of the last visit for the last subject in the study. A participant is considered to have completed the study if they have completed all steps of the protocol.

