### 2.5. Study Procedures

Step 1. Patients were screened and recruited during hospitalization in the Cardiovascular Department of IRCCS MultiMedica (Sesto San Giovanni—MI, Italy) or Cardiac Rehabilitation Unit of IRCCS ICS Maugeri (Bari—BA, Italy). The main clinical and demographic data were collected for each patient. The day before discharge, patients performed a 6 min walk test, gave a blood sample to test for molecular biomarkers and underwent a frailty evaluation on both the EFT and SPPB scales. Depression, quality of life, cognitive status, nutritional status, and adherence to medical therapy were evaluated with adequate tools. Blood samples were collected to identify biomarkers able to identify frailty and predict its progression.

Step 2. Before discharge, all enrolled patients were randomized in a 1:1 ratio to intervention (Group A) or usual care (Group B). Group A followed a multidisciplinary home-based TR program while Group B was referred to general practitioners (GPs).

Step 3. The home-based TR program was implemented in Group A patients. Group B was referred to GPs according to usual care. During step 3, clinical outcomes and adverse events were collected.

Step 4. After at least 3 and at most 6 months of follow-up, patients underwent final evaluation; the procedures of step 1 were repeated. Study procedures are summarized in Supplementary Table S1.

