### 2.18. eHealth Home-Based CR Program

A multidisciplinary home-based CR program was implemented for Group A patients. The program lasted a maximum of 6 months; it was coordinated by a cardiologist and it was based on a multidisciplinary intervention by different healthcare providers: a nurse (case manager), physiotherapist, psychologist, and dietician.

The protocol was shared between the investigators involved in the two centers and was developed based on the most recent guidelines [5]. The online platform used for the intervention had a pre-specified list of questions and items to check, including the vital parameters to be collected at each visit, in order to maximize standardization and the fidelity of the programs between the two centers involved.

In the present study a synchronous model of cardiac TR, based on a real-time interaction between the patient and healthcare provider, was used. The advantages of this approach are that it allows a very close follow-up and better program personalization.

The core of the TR program was represented by scheduled video-calls with the patient (2 per week, 30–45 min duration each) by the nurse and physiotherapist focused on: education and cognitive training, exercise training session along with physiotherapy counseling once a week, assessment of healthy lifestyle, risk factor control, medication adherence and therapeutic targets. A video-call with a psychologist and dietician for psychosocial and nutritional counseling was provided at least once per fortnight. A social assistant was involved as needed by the nurse case manager.

The video-call was done by cell phone, tablet, or PC according to the patient’s preference.

For monitoring medication adherence and fall risk, one tool, i.e., text messaging, smartphone applications, or other electronic devices, tailored to the patient’s characteristics was applied. If applicable, an initial in-home visit to assess fall risk elements was also performed and a digital health alarm system to alert caregivers in case of physical discomfort was provided.

The program also included unscheduled calls from the patient in predefined time slots in case of need.

A pulse oximeter and a portable one-lead electrocardiograph for the telemonitoring of vital signs were available, and patients were able to call and be assisted in the case of urgent need or emergency, according to the internal standard operating procedure of each site.

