### 2.24. Lost to Follow Up

A participant was considered lost to follow-up if they were repeatedly unable to be contacted by the study site.

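### Section 2.23 lets unblinded investigators withdraw a patient from the study, not only from the programme, for poor compliance, which can remove Group A's poor adherers before frailty is measured

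*Protocol article*

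**What the plan says.** Under section 2.23 a participant may leave at their own request, or "may be withdrawn at any time at the discretion of the investigator for safety, behavioral, compliance, or administrative reasons". The section title alludes to a modified follow-up, but the text beneath it describes only leaving the study.

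The arms differ in what there is to comply with. Section 2.18 builds Group A's programme on "scheduled video-calls with the patient (2 per week, 30–45 min duration each") plus exercise training. For the other arm, section 2.5 says "Group B was referred to GPs according to usual care". Section 2.1 states that "the trial was not blinded" and adds that the investigators who assess frailty also helped to develop the programme.

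Section 2.22 restricts the frailty-prevalence and EFT analyses to people with EFT at baseline and follow-up, and the SPPB analysis to people with SPPB at both times. Regression imputation is planned for the other covariates only.

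**The concern.** After randomisation, a Group A patient who stops logging in can be judged non-compliant and withdrawn from the study. A Group B patient in the same state of health has no programme to fail. The exclusion criteria in section 2.4.2 show what compliance means here: they illustrate it by the ability to use the eHealth device.

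The decision is discretionary, has no stated criteria, and is made by staff who know the allocation. If a withdrawn patient is not assessed at Step 4, section 2.22 drops that patient from the prevalence, EFT and SPPB analyses. If poor adherers are frailer than the rest of Group A, the remaining Group A patients look less frail than the arm that was randomised, and the comparison moves towards TR. Later deaths, hospitalisations and falls in these patients could also go unrecorded.

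**Working it through.** **Plan's own figures (section 2.20 and Discussion).**
- Prevalence, 34% vs 21%, two-sided alpha 5%, power 80%, pooled variance: n per arm = [1.96·√(2·0.275·0.725) + 0.8416·√(0.34·0.66 + 0.21·0.79)]² / 0.13² = 184.01, rounded up to 185, so 370 in total. This matches the stated 370.
- Mean EFT, 1.95 vs 1.25, SD 1.25, power 90%: n per arm = 2·(1.96 + 1.2816)²·1.25² / 0.70² = 67.01, rounded up to 68, so 136 in total. This matches the stated 136.
- Power for prevalence with 103 per arm: 55.2%, against the stated 55%.

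The planned effects of 13 points and 0.70 EFT units are therefore sound yardsticks. They neither prove nor disprove the concern.

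**Sensitivity calculation.** From the documents: 103 patients per arm, Group B final prevalence 34%, EFT SD 1.25. My assumptions: no true effect, Group B complete, a share w of Group A withdrawn, frailty prevalence q among those withdrawn, or their mean EFT higher than the whole-arm mean by e.

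- Observed prevalence in A = (0.34 − w·q)/(1 − w). The spurious difference is 0.34 minus this.
- Spurious EFT difference = w·e/(1 − w).

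Examples: w = 10%, q = 50% gives (0.34 − 0.05)/0.90 = 32.2%, a difference of 1.8 points. w = 22%, q = 70% gives (0.34 − 0.154)/0.78 = 23.8%, a difference of 10.2 points. w = 22%, e = 1 gives 0.22/0.78 = 0.28.

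| w (patients of 103) | Points, q = 34% | q = 50% | q = 60% | q = 70% | EFT, e = 0.5 | EFT, e = 1.0 |
|---|---|---|---|---|---|---|
| 5% (about 5) | 0 | 0.8 | 1.4 | 1.9 | 0.03 | 0.05 |
| 10% (about 10) | 0 | 1.8 | 2.9 | 4.0 | 0.06 | 0.11 |
| 15% (about 15) | 0 | 2.8 | 4.6 | 6.4 | 0.09 | 0.18 |
| 22% (about 23) | 0 | 4.5 | 7.3 | 10.2 | 0.14 | 0.28 |

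For q from 50% to 70%, the chance of a false positive at nominal 5% is 5.2–5.9% at 5% loss, 5.8–9.1% at 10% and 9.8–31.8% at 22%. For EFT with e from 0.5 to 1.0 it is 6.1–9.5% at 10% loss and 11.8–32.9% at 22%.

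The 22% row borrows the plan's overall dropout allowance and places it in Group A alone, so it is a severe case for one arm. These are unadjusted comparisons. The planned adjustment for sex and baseline SPPB would remove the part of the bias that those variables explain. SPPB follows the same formula, but the article gives no planned SPPB difference to set it against.

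**The case against.** The strongest reply is that section 2.23 is one permissive sentence, worded for any participant, in an article that condenses a deposited protocol. The Figure 1 caption, section 2.1 and Step 4 in section 2.5 describe the follow-up evaluation for enrolled patients generally, without tying it to adherence. Event collection is not limited to one arm either: "During step 3, clinical outcomes and adverse events were collected". All this is true, and the article does not state that withdrawn patients go unassessed. It does, however, state a rule for leaving the study on compliance grounds, and nothing in the text shown keeps such patients in follow-up.

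A reader might go further and infer that all the exit rules act on Group A alone. The documents do not support that:
- Own request and the safety, behavioural and administrative grounds are open to both arms. Compliance with study assessments also concerns both.
- The loss-to-follow-up rule in section 2.24, "A participant was considered lost to follow-up if they were repeatedly unable to be contacted by the study site", is neutral between arms. Two calls a week give Group A more chances to be missed but also more chances to be reached. Group B, with no described call schedule, could be lost more easily.
- The completion rule in section 2.3, "A participant is considered to have completed the study if they have completed all steps of the protocol", weighs more on Group A because Step 3 is the programme there. But section 2.22 selects on available EFT or SPPB, not on completion, so a patient who stops TR and attends Step 4 is analysed.

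Nor do the documents show that bias has occurred. The only non-death dropouts reported so far are two controls, lost before completing baseline examinations or questionnaires. That says little about compliance during follow-up, but it gives no support to a Group A excess.

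**Conclusion.** The point holds in a limited form. As written, sections 2.23 and 2.22 together allow poor adherers to disappear from the intervention arm only, on an open-label and discretionary judgement, before EFT and SPPB are measured. The direction favours TR only if those withdrawn are frailer than the rest of Group A and losses in Group B do not offset them.

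Under the assumed one-sided losses of 10–22%, the spurious difference is about 2–10 points in prevalence (planned 13) or 0.06–0.28 in mean EFT (planned 0.70). At 5% loss it is at most about 2 points or 0.05 units, and it is zero if those withdrawn resemble their arm. EFT matters more than prevalence here, since section 2.2.1 now treats prevalence as exploratory. The number withdrawn, their frailty and the completeness of Group B are assumptions, so the true size and net direction are unknown. Claims that the bias is established, or that the contact and completion rules create it too, go beyond the text.

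**What to change.** Amend section 2.23 so that compliance, behavioural or administrative reasons can end participation in the TR programme only. The patient then stays in the study, is invited to Step 4 on the same schedule as Group B, and remains in event follow-up unless consent is withdrawn. Patients already withdrawn for compliance who are still inside their 3–6 month window should be invited to Step 4. Report withdrawals by arm and reason, which remains possible for patients whose window has closed. If the deposited full protocol already keeps withdrawn patients in follow-up, saying so in the article is enough.

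The cost is a short amendment and a few extra calls by existing staff. Including poor adherers may make the estimated effect smaller. The benefit is limited by timing: recruitment ran to December 2025 and follow-up lasts at most six months, so the last windows close about June 2026.
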